### Who will take informed consent? {26a}

Recruitment will be overseen by the SMARTERscreen steering group (JM, MJ, BG, JE, PC, and JT) who will report to the investigators.

#### General practice informed consent for the trial

The project officers will obtain informed consent from all eligible and interested general practices. All GPs in the practice need to agree to be involved, but only one consent form will be required from each practice. Two senior practice staff—usually the Practice Manager and Principal GP or their delegate—will complete the consent form on behalf of the general practice. This is common practice in general practice research.

The practice will be provided with copies of the plain language statement and a signed consent form for their records.

#### Patient-informed consent for the trial

Patient consent is not being sought because only de-identified data will be collected for the analysis and only aggregated results will be published. Patients provide consent for the use of their health information when they join a practice, and this includes data from sites that provide access to the Provider Digital Access (PRODA) portal, an online identity verification and authentication system that lets GPs securely access government online services including the NCSR [16]. Recently, the NCSR have built a portal (the Health Provider Portal—‘HPP’) so the data transfer between practice and the NCSR can occur in real time, for example during a consultation. Using the HPP, the GP can check if a patient is due for screening. To avoid having to do this for every eligible individual (potentially 100 s of patients per practice), we have developed a way for the practice to do this in bulk using a secure file transfer portal (SFTP). To ensure the secure transfer of data between the practice and the NCSR has been established, we require the practice to have the NCSR HPP installed as part of their involvement in the trial. The transfer details are described below.

### Additional consent provisions for collection and use of participant data and biological specimens {26b}

Not applicable. No biological specimens will be collected.

### Interventions

#### Explanation for the choice of comparators {6b}

Control arm practices: GPs will continue practising usual care, complying with bowel cancer screening guidelines as defined by the Royal Australian College of General Practitioners Red Book for Preventive Activities in General Practice and opportunistically discussing bowel cancer screening with their patients [18].

#### Intervention description {11a}

The trial is comparing two interventions.

*Intervention 1*: ‘SMS only’—an SMS will be sent from the general practice to prompt patients to do the NBCSP kit. The SMS contains a personalised greeting to the patient using their first name only, the general practice name and telephone number, and a GP endorsement of the NBCSP (Fig. 1). The SMS will be delivered by GoShare, an online tool developed by Healthily, a company that sends timely educational resources to consumers directly from their general practice via SMS [19]. Within the SMS, participants will be provided the opportunity to opt out of receiving any further health promotion SMS from Healthily, but this will not stop them from receiving other SMS messages from their practice (e.g. appointment reminders). The SMS wording is: ‘Hi [insert first name of patient here], Your free bowel cancer screening kit will arrive in the post soon. [insert general practice name here] strongly encourages you to do this test. Call us on [insert general practice phone number here] if you have any questions. Reply STOP to opt out.’ 3.

**Fig. 1 Fig1:**
[figure not shown]
Intervention 1, the SMS only

*Intervention 2*: ‘SMS bundle’—an SMS with a weblink will be sent from the general practice to prompt patients to do the NBCSP kit (Fig. 2). The SMS will consist of the same text message as Intervention 1 but with an added weblink to the following motivational and instructional materials: a GP endorsement of the NBCSP, a consumer co-designed video of relatable people talking about why it is important to participate in the NBCSP, an animated instructional video to provide simple step-by-step instructions on how to complete the NBCSP kit, and a link to more information about the NBCSP. The wording is: ‘Hi [insert first name of patient here], Your free bowel cancer screening kit will arrive in the post soon. [insert general practice name here] strongly encourages you to do this test. We also recommend you watch these videos [weblink to videos inserted here]. Call us on [insert general practice phone number here] if you have any questions. Reply STOP to opt out.’ The first part of the weblink shows a similar message from the general practice with the GP logo. The second and third parts include video material co-designed by Cancer Council Queensland, tested with 200 consumers and a group of experts, led by BG and the SMARTERscreen steering group. The motivational video (second part of the bundle) is a montage of three people (real consumers) discussing the benefits of doing the NBCSP kit. The instructional video (third part of the bundle) is an edited version from the NBCSP and demonstrates how to do the test (unpublished). There is also a link to more information about the NBCSP.

**Fig. 2 Fig2:**
[figure not shown]
Intervention 2, the SMS bundle with the SMS with a weblink (i) and contents (ii–iv)

#### Criteria for discontinuing or modifying allocated interventions {11b}

General practices can withdraw from the SMARTERscreen trial at any time without providing a reason, but after the practices are randomised, we will not be able to exclude their patient data as they are collected in a de-identified form and will be included as part of the main analyses even if they receive part or none of the intended intervention. Patients can opt out of receiving any more SMS from Healthily by replying “STOP” to the text message. This will not stop them from receiving messages from their GP, only block future messages from Healthily. Posters will be in the waiting room of all practices to inform patients about the trial and to let them know they can ask not to be included in the trial; this will only be possible prior to de-identified data collection from the practice EHR.

Patients who are eligible to receive a NBCSP kit at the beginning of the intervention period after randomisation occurred but are subsequently not sent a FIT kit during the trial intervention period (coded as “FIT kit not sent’) will be excluded from the primary analysis. Reasons patients are not sent a kit during the 6-month intervention period may be as follows: (a) they opted out of receiving kits from the NBCSP; (b) they put their NBCSP kits on temporary hold; (c) they have a recently recorded bowel cancer diagnosis; (d) they have recently had a colonoscopy (and are not due screening); or (e) they have a record of having had a recent FIT test elsewhere.

#### Strategies to improve adherence to interventions {11c}

The SMARTERscreen project officers will be in regular contact with general practice staff during the data collection and transfer, and to manage and schedule SMS to be sent through the GoShare platform for intervention practices. Training and a comprehensive manual will be provided to maintain consistency and quality of the intervention delivery and data collection for all participating general practices.

#### Relevant concomitant care permitted or prohibited during the trial {11d}

There is no concomitant care that will be prohibited during the trial.

#### Provisions for post-trial care {30}

At the conclusion of the trial, the Healthily GoShare messaging platform will be provided free of charge to all participating general practices for 6 months. The SMARTERscreen SMS and SMS bundle with a training manual and ‘cheat sheets’ will be available ongoing. SMS messages will be subsidised by the project for 6 months for up to 260 eligible patients.

No additional post-trial care will be required as all practices will be working within the recommended clinical guidelines for CRC screening during the trial period [18].

#### Outcomes {12}

The primary outcome is the difference in all three pair-wise comparisons between the three arms in the proportion of eligible patients who were sent a NBCSP kit and who have a date recorded for when the FIT kit was received by the NBCSP and recorded in the NCSR (indicating they have returned their kit) within 6 months from the date when the kit was due to be sent to each participant. For patients who were sent the NBCSP kit, the outcome variable will be coded as having either a ‘FIT kit returned’ or ‘FIT kit not returned’. ‘FIT kit returned’ will include patients who have a date for the returned NBCSP kit in the NCSR registry within 6 months of when their kit was due. ‘FIT kit not returned’ will include patients who were sent a kit but they either do not have a date recorded, or the date is outside the 6-month range. After randomisation has occurred, patients who were eligible to receive a NBCSP kit at the beginning of the intervention period but were subsequently not sent a FIT kit during the trial intervention period will be coded as ‘FIT kit not sent’. This will include patients who were not sent a kit during the 6-month intervention period for a number of reasons: (a) they opted out of receiving kits from the NBCSP; (b) they put their NBCSP kits on temporary hold; (c) they have a recently recorded bowel cancer diagnosis; (d) they have recently had a colonoscopy (and are not due screening); or (e) they have a record of having had a recent FIT test elsewhere. These people will be considered ineligible.

#### Economic evaluation outcome

The economic model-estimated cost-effectiveness of both sending a GP practice-endorsed SMS with/without additional motivational material to people before they are due to do their NBCSP kit to increase the uptake of the NBCSP and the SMS intervention compared with usual care.

#### Measures for adherence to intervention

Proportion of individuals sent an SMS and was delivered in Intervention 1Proportion of individuals sent an SMS bundle and was delivered in Intervention 2For Intervention 2 only; proportion of individuals who receive the SMS bundle, who:Open the SMS link one or more timesView the motivational video one or more timesView the instructional video one or more timesView the NBCSP webpage information one or more timesFor Intervention 2 only; of individuals who open the SMS bundle, count of the:Number of times the SMS link is openedNumber of times the instructional video is viewedNumber of times the motivational video is viewedNumber of times the NBCSP webpage information is viewed.Number of people who opt out

#### Participant timeline {13}

See Fig. 3.

**Fig. 3 Fig3:**
[figure not shown]
The timeline for recruitment and data collection

#### Sample size {14}

Sample size was based on 80% power for an overall two-sided significance level of 5% (alpha), and an intraclass correlation coefficient (ICC) of 0.01. Planned primary comparisons are the two intervention arms (SMS only and SMS bundle) with the control arm, respectively, and the SMS only intervention with the SMS bundle. The Holm-Bonferroni correction was used to control the family-wise error rate across three pairwise comparisons. Thus, for the purposes of the sample size calculations, we conservatively set the alpha at 0.017. We assumed that 34% of patients in the control arm will have completed their FIT, based on the National screening data [20]. Sixty-three practices with an average of 260 of eligible patients per practice (standard deviation = 197; range 51 to 753; coefficient of variation = 0.76) [15] will be sufficient to detect a difference of 10% absolute increase in participation in the NBCSP within 6 months from when the NBCSP kit is due between each intervention arm (SMS only and SMS bundle) and control arm (44% vs 34%), respectively; and to detect a smaller difference of 7.5% (44% vs 51.5%) between the SMS only and SMS bundle intervention arms. The total of 63 practices allows for an additional practice per arm for potential loss of practices due to closures or merges. A national 10% increase in screening participation would prevent 27,000 bowel cancers and 16,800 deaths and is associated with an additional $200 million in costs over current screening levels over the next 20 years [4]. We anticipate that adding the weblinks to motivational and instructional videos in the SMS would have a smaller additional effect on increasing screening participation compared to a SMS only.

#### Recruitment {15}

General practices will be identified for recruitment in the following ways: through the Department of General Practice and Primary Care at the University of Melbourne primary care practice-based research and education network, which includes general practices in Victoria and a smaller number in Queensland who are engaged with any research and/or teaching with the University of Melbourne; through the Queensland Cancer Council database of general practices who have expressed an interest in being involved in research; through the research team’s professional networks; snowballing based on advice from other practices; and cold-calling practices identified through web-based searches.

The recruitment will involve initially contacting the general practices by telephone to introduce the project and to organise a face-to-face meeting to explain the trial in more detail. If eligible (see above) and interested, the project officers will arrange to meet with the general practice staff—either face-to-face or on Zoom—to double-check the practice meets the eligibility criteria and explain the trial requirements including details about the intervention. The project officers will ensure all staff know about the trial before it starts and set up a process for staff to contact them if they have questions or to let them know if there are any staff changes during the trial. Two senior practice staff will then provide consent on behalf of the general practice.

Patients will not be individually recruited as the research team will only have access to de-identified data from the general practice that has been collected from the NCSR.

## Assignment of interventions: allocation

### Sequence generation {16a}

The unit of randomisation will be the general practice (cluster). Once all general practices have been consented and eligible participants have been identified within practices, the eligible patient lists will be sent to the NCSR to be enriched. Once the data have been sent back to the practices, the general practices will be randomly allocated with a 1:1:1 ratio to either the control or one of the two intervention arms. Randomisation will be stratified by geographical location (metropolitan/larger regional and rural/smaller regional) and state (Queensland and Victoria), and each stratum will have a computer-generated random allocation sequence with random permuted block sizes.

General practice location will be stratified as either metropolitan/larger regional if located in MMM 1–3 and rural/smaller regional if located in MMM 4–6 [17]. If two practices that share EHR are located across the two geographic locations (MMM1-3 and MMM4-6), they will be allocated to the MMM category where the main practice is located for randomisation.

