### Implementation {16c}

Following general practices' consent, and after patient data extraction from the EHR and linkage with NCSR records, the statistician (PC) will randomly allocate the general practice using the random allocation schedule and inform the project officers of the randomisation status of each general practice using the uninformative codes. Using the key for the uninformative codes, the project officers will inform the practice manager of each general practice their allocated study arm allocation both verbally and in writing. The project officers will keep a record of the practice’s unique identifier code, practice name and allocated trial arm status, which will be securely stored and only accessible by the project officers.

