## Assignment of interventions: blinding

### Who will be blinded {17a}

The statisticians and the SMARTERscreen steering group members not involved in the delivery of the intervention will be masked to the general practices allocated trial arm until after the analysis of the primary outcome. General practice staff will not be blinded as to the allocation of the randomisation as this will not be possible.

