#### The method (Fig. 4)

##### Step 1

The eligible patient list will be collected from each general practice EHR using a bespoke Structured Query Language (SQL) query. The list will be saved as a comma-separated values (.csv) file securely on the practice computer, with a name specific to the study identifier of the practice (practice ID) and the date of extraction (Dataset 1).

##### Step 2

The practice manager will add three columns of data including (1) a column with a Provider number for the principal GP for that practice, (2) a column with a unique trial ID code for each patient (e.g. GP0010001), and (3) a column with a unique practice ID code for each practice (e.g. GP001) (Dataset 2).

##### Step 3

This dataset will be saved as a.csv file and uploaded to the NCSR using a secure file transfer protocol (SFTP).

##### Step 4

Once the NCSR have the.csv file (Dataset 2), they will match the patients in the NCSR by date of birth, Medicare number, and name. The.csv file will be enriched with five additional columns of data for each person: one for the date they returned their last NBCSP kit (or blank if they have not returned one before) [‘Date_kit_returned’], one with the date their next NBCSP kit is due [‘Date_Kit_Due’], one if the NCSR cannot match patients’ identifying data with the register’s records [‘1’ if records match with NCSR database, ‘0’ if data in the.csv file does not match the register], one calculating the date the SMS will be sent [‘Date SMS is due’ which will be calculated as the (‘Date the NBCSP kit is due’ − 14 days)], and one calculating the patient’s age at the time when their kit is due [‘Age in months when kit is due’, which will be calculated as (= ‘Date the NBCSP kit is due’ − ‘Date of Birth’ in years, multiplied by 12)].

The NCSR will then save a.csv file (i.e. NCSR dataset) for every practice (Dataset 3).

##### Step 5

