The intervention period will be for 6 months (26 weeks). The staff (funded by the research team) in the NCSR will then generate datasets for each week of the intervention period that include all patients who are due a SMS that week based on ‘Date SMS is due’ (Dataset 4). This date will be calculated so that the SMS will be sent on a Sunday for kits due 3 days on either side of that date. Each dataset will only include the Unique Record ID, Patient’s first name, and mobile number. The name of the file will identify the GP practice and the date when the SMS are due to be sent. All 26 NCSR datasets created for each general practice will be saved as separate encrypted.csv files and sent using a secure file transfer portal to the general practice.

The general practices in the intervention arms will be instructed to transfer the NCSR.csv datasets that have been separated into 26 weekly files. These will then be uploaded to the GoShare platform and scheduled for sending the SMS/SMS plus bundle on the Sunday they are due (approximately 2 weeks prior to the kit being sent). The control arm practices will not be provided access to the NCSR datasets until the end of the trial.

##### Step 6

At the end of the intervention period:

Using the Dataset 3 created in Step 5, the NCSR will add an additional variable ‘Date the kit was returned’ for each person. If there is no date for a returned kit, then a reason as to why the person was not sent the kit will be added in a separate field—this will happen if there has been a concurrent event (e.g. patient had a colonoscopy, opted out or deferred their screening, was diagnosed with colorectal cancer, or had a FIT test from elsewhere recorded), or the field will be left blank with the assumption that the person did not return the kit within 6 months of the due date of the NBCSP kit. The NCSR dataset (Dataset 5) with the added kit return dates will be stored on the NCSR secure server as a.csv dataset and downloaded by secure file transfer by the practice when needed.

##### Step 7

Dataset 6 will be created using Dataset 5, where individual identifying information (such as name, address, and mobile number) will be removed, and provided to the research team for analysis. The dataset may be securely transferred to the research team via the GP Practice (once the records have been de-identified) or directly from NCSR.

##### Step 8

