### Data management {19}

Data management will be overseen by the project officers and under the supervision of the SMARTERscreen steering group, and statistician in accordance with the statistical analysis plan (SAP). The project officers will be responsible for training and supervising the general practice staff to extract the eligible patient list from the EHR, save it securely, name it according to the naming protocol, upload it to the NCSR, download the revised list from the NCSR, and then upload the de-identified lists with the results to the research staff (Fig. 4). The NCSR staff member will be supervised and overseen by the SMARTERscreen steering group to manage the data at the NCSR including the secure transfer to and from the general practices.

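### Randomising after register data return to all practices conflicts with withholding those data from control practices, and no means of withholding is stated

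*Protocol article*

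**What the plan says.** All places are in the protocol article.

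- **Sequence generation {16a}.** Practices consent, eligible patients are listed, and the lists go to the register for enrichment. Then: "Once the data have been sent back to the practices, the general practices will be randomly allocated with a 1:1:1 ratio".
- **The method (Fig. 4), Step 4.** The enriched list (Dataset 3) carries for each patient, among other columns, "one with the date their next NBCSP kit is due" and the date of the last returned kit. The register saves one such file per practice.
- **The method (Fig. 4), Step 5.** "All 26 NCSR datasets created for each general practice will be saved as separate encrypted.csv files and sent using a secure file transfer portal". The named recipient is the practice. Each weekly file holds a record ID, first name and mobile number; the file name gives the practice and the SMS date. Intervention practices load the files to the messaging platform. The step ends: "The control arm practices will not be provided access to the NCSR datasets until the end of the trial".
- **Implementation {16c}.** Allocation comes "after patient data extraction from the EHR and linkage with NCSR records". Return of lists to practices is not mentioned here, nor in Concealment mechanism {16b}.
- **Data management {19}.** Practice staff are trained to "download the revised list from the NCSR", with no arm or time attached.
- **Who will be blinded {17a}.** "General practice staff will not be blinded as to the allocation of the randomisation as this will not be possible".

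**The concern.** Step 5 shows that the investigators meant to keep the register information from control practices. The order in {16a} works against that, because data returned before allocation go to practices that later become controls.

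A control practice holding the lists would be well placed to prompt its own patients. Staff learn the intervention details before consent (Recruitment {15}) and know their allocation. Every eligible patient has a mobile number on file and has not opted out of practice messages (Eligibility criteria {10}). Prompting of this kind would move usual care towards the intervention. The intention-to-treat analysis would rightly keep such a practice in the control arm, and the listed adherence measures cover only the two interventions, so they would not reveal it. Both estimated effects against control would then be too small. The arm-specific participation rates also feed the Policy1-Bowel model, so the understatement would carry into the economic results.

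**Working it through.** **1. The passages side by side.**

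- Under {16a} the order is: extract, enrich, return to practices, randomise. At the return step there are no arms, so all 63 practices are recipients.
- Under {16c} the order is: extract, link, randomise. Nothing needs to reach a practice before allocation, so this order is compatible with withholding files from controls.
- Within Step 5, the weekly files go to each practice with no arm limit, and control practices are then denied access. The two statements are compatible only if delivery is separated from access, for instance by a retained key. The files are encrypted, but no section says who holds the key or that control practices are refused it.
- The line in {19} could mean the baseline list or the end-of-trial list. It does not settle the matter.

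So {16a} is the sentence out of line with {16c} and with the last sentence of Step 5, and Step 5 lacks the mechanism it needs.

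**2. What a control practice would gain.** Names and mobile numbers come from its own records. The new element is timing in bulk: explicit due dates if Dataset 3 is what is returned, or the approximate due week if only weekly files are opened, since the SMS falls about 14 days before the kit is due.

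**3. The plan's own sample size.** Inputs from Sample size {14}: two-sided alpha 0.017, 80% power, ICC 0.01, mean cluster size m = 260, CV 0.76, and 21 practices per arm of which one is a reserve.

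- Design effect = 1 + ((0.76² + 1) × 260 − 1) × 0.01 = 5.09.
- Unclustered n per arm = [z(1−α/2)·√(2p̄(1−p̄)) + z(0.80)·√(p₁(1−p₁) + p₂(1−p₂))]² / (p₁ − p₂)², where p̄ is the mean of p₁ and p₂.
- 34% vs 44%: n = 495; 495 × 5.09 / 260 = 9.7 practices per arm.
- 44% vs 51.5%: n = 924; 924 × 5.09 / 260 = 18.1 practices per arm.

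The second comparison is the binding one. With 20 practices per arm its power is 84.4% (81.3% with a noncentral t on 38 df), so the stated size agrees with its inputs. The 10-point comparison has 98.8% power.

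**4. Illustrative dilution.** The documents give no contamination rate. Assume that a share c of control patients gets the full 10-point SMS effect. The control rate becomes 34% + 10c points and the difference 10(1 − c) points. Power with 20 practices per arm, alpha 0.017, same design effect, normal approximation:

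| c | Control rate | Difference | Power vs control |
|---|---|---|---|
| 0 | 34% | 10 points | 98.8% |
| 10% | 35% | 9 points | 96.3% |
| 20% | 36% | 8 points | 90.5% |
| 30% | 37% | 7 points | 79.9% |
| 50% | 39% | 5 points | 46.3% |

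The control arm does not enter the SMS only versus bundle contrast, so that comparison is unaffected at any c.

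**The case against.** The strongest reply is that the safeguard is already written down. Step 5 states that controls have no access, {16c} needs only linkage before allocation, and the weekly files are encrypted. Sending a file is not the same as giving access to it. No numbered step sends Dataset 3 to practices before the trial ends; Step 6 describes Dataset 5 as held on the register's server and downloaded when needed. On this view {16a} is one loosely worded sentence.

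Further, every practice must install the register portal, so a control GP can already look up a single patient's due status, and opportunistic discussion is part of usual care. Control practices are also promised the platform and subsidised messages after the trial, which weakens any motive to act early.

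Much of this stands. A reader might infer that the passages cannot be reconciled under any arrangement, or that the control arm will be contaminated. The documents support neither: encryption leaves a way for Step 5 to be carried out, and no passage reports or predicts prompting by control practices. What remains is that {16a} makes return of the data a condition for allocation, and nowhere is it said how access is then withheld. Single-patient look-up is no substitute for a bulk list; the section on patient consent explains that the bulk route was built to avoid checking each individual.

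**Conclusion.** The conflict over order and access is real, and the protocol should resolve it. Its consequence is a risk, not a demonstrated bias. If {16a} is followed and nothing blocks the files, unblinded control practices would hold bulk information on who is due and roughly when, and both comparisons with control could be diluted towards zero.

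The size cannot be derived from the documents. The table in the working rests on an assumed share of control patients and an assumed full SMS effect among them. A reader might infer that the trial loses its power; that is not supported, because power against control stays near or above 80% until that share reaches roughly 30%. The more relevant harm is an understated effect, which arises at any share above zero. If in practice the lists were withheld as Step 5 says, {16a} still misdescribes the procedure.

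**What to change.** - In Sequence generation {16a}, let randomisation be triggered by the register's confirmation that linkage is complete and Dataset 3 is locked. This agrees with {16c} and still fixes the patient lists before allocation.
- In Step 5 and in Data management {19}, state that weekly files, or their decryption keys, are released only after allocation and only to intervention practices, and that control files are withheld until the end of the trial. Say in {19} which list is downloaded and when.

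The cost is a few sentences and a change in the order of release. The intervention starts only after randomisation (Trial status), so this need not delay it. There is one small downside: releasing files by arm could reveal allocation to the register staff who supply the primary outcome. The project officers already hold the allocation key, so they should control the release or the decryption keys. They should not hold the files themselves, since Confidentiality {27} limits identifiable data to practice and register staff.
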